### Functional assessments

Standardized testing to evaluate olfaction, cognition, lung function and functional capacity was administered by trained research personnel. Smell was evaluated using the Brief Smell Identification Test (BSIT) which requires the identification of 12 odors from a scratchable booklet. In healthy older individuals, impaired olfaction on BSIT predicts cognitive decline (20). Cognitive performance was ascertained during 30–40 min sessions from the NIH toolbox with patients completing 5 modules including the Picture Sequence Memory Test, List Sorting Working Memory Test, Dimensional Change Card Sort Test, Auditory Verbal Learning Test and Oral Symbol Digit Test. Hand-held spirometry measured forced expiratory volume in 1 s and forced vital capacity during 3 repetitions. Six-minute walk test (6MWT) was performed to assess aerobic endurance using standardized instructions (21). Patients also performed a 25-foot timed walk test to identify potential neurologic disease affecting mobility (22).

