*Skeletal Muscle*: Skeletal muscle T1 and fat content (intermuscular, intramuscular, and subcutaneous) was measured using a muscle-specific variant of the SR-CSE approach. Typical image parameters include 5 axial slices (centered 17 cm superior to the distal head of the femur) with a 3.5 mm thickness (12.5 mm gap), [2.51 3.51 4.51 4.78 5.78 6.78] ms echo times, 9.0 ms repetition time, 30° flip angle, rate 2 parallel imaging (GRAPPA) for a 41 s acquisition. A custom machine learning segmentation approach will be used to identify subcutaneous fat, intermuscular fat, muscle and bone regions. Calculated parameters included volumes of subcutaneous fat, muscle, intermuscular fat, intramuscular fat (fat content in the muscle region), muscle T1 and muscle T2* (from the muscle region).

*Lungs*: Lung images were acquired using a custom non-Cartesian ultrashort TE (TE = 70 μs) yarnball *k*-space trajectory with free-breathing acquisitions (31). Free-breathing data collection was completed in 120 s with reconstruction of 2 mm × 2 mm × 2 mm resolution images at 20 respiratory phases over the breathing cycle. Global lung water density at functional residual capacity (minimum lung volume) was quantified with a user-independent machine learning lung segmentation approach. Additionally, the presence of patchy pathology was identified using an automated quantitative approach employing radiomic analysis of the lung parenchyma. We used a previously trained deep learning model to segment the lung parenchyma of our images (32). Once the parenchyma of each lung is isolated, intensities are discretized into 5% lung water density bins to simplify image features prior to feature extraction. Finally, 40 radiomic texture features are computed in three dimensions for each lung using a MATLAB (MathWorks, Natick, MA) toolkit (33).

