### Study outcomes

Primary outcomes include patient reported symptom burden and organ injury metrics as assessed by functional performance evaluations, serum biomarkers and MRI tissue characterization (Table 1). Secondary outcomes include imaging and circulating biomarkers of cardiovascular health (Table 2). Clinical events at 12 months will be collected though chart review to ascertain relevant clinical outcomes including incident diabetes and cardiovascular disease.

**Table 1 tab1:** Summary of organ injury outcomes.

Organ	Functional performance	Circulating biomarkers	Magnetic resonance
LUNG	Spirometry 6 min walk testing	None	Lung water density Lung lesions (radiomic analysis)
CARDIAC	6 min walk testing	Troponin I B-type natriuretic peptide	LVEF Myocardial T1 Myocardial T2
BRAIN	Cognitive testing	None	Brain volume Brain lesions (FLAIR and DTI) Susceptibility and iron mapping
HEPATIC	None	AST ALT GGT LDH Total bilirubin	Hepatic T1 Hepatic T2*
RENAL	None	Electrolytes Creatinine	Renal T1
SKELETAL MUSCLE	6 min walk testing	None	Skeletal muscle T1 Skeletal muscle T2*

AST, aspartate aminotransferase; ALT, alanine aminotransferase; LDH, lactate dehydrogenase; GGT, gamma-glutamyl transferase; LVEF, left ventricular ejection fraction; FLAIR, fluid attenuation inversion recovery; DTI, diffusion tensor imaging.

**Table 2 tab2:** Summary of cardiovascular health outcomes.

	Circulating biomarkers	Magnetic resonance	Clinical events
CARDIAC	Troponin I B-type natriuretic peptide	LVEF Myocardial T1 Myocardial T2	Cardiovascular death or hospitalization
CARDIOMETABOLIC	C-reactive protein White blood cell count Glucose Insulin Lipid profile	Visceral adipose tissue Hepatic fat Intramuscular fat Intermuscular fat	Incident diabetes Incident dyslipidemia Incident hypertension

LVEF, left ventricular ejection fraction.

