### Statistical plan

The Shapiro–Wilk normality test will be used to test the normal distribution of continuous variables which will be expressed as mean ± standard deviation or median (25th, 75th percentile), as appropriate. Categorical variables will be expressed as frequency and percentage. When comparing data between recovered COVID-19 patients and healthy controls, chi-square testing or Fisher’s exact test will be used for categorical variables and two sample t-test or Mann–Whitney U test used for continuous variables, as appropriate. Functional performance, biomarker results and imaging metrics indicative of organ injury will be compared across groups of symptom severity (none, mild, moderate and severe) within the recovered COVID-19 patients using a one-way analysis of variance with *post hoc* pairwise comparisons by either Tukey’s or Games-Howell tests, depending on equality of variances. Pearson correlation analyses will evaluate relationships between MRI measures of tissue injury and functional performance metrics. Univariable Cox proportional regression of clinical outcome will be performed in all serum and imaging parameters. In the multivariable Cox proportional hazard analysis, all non-collinear parameters of interest with univariable *p*-value < 0.2 will independently test for their association with composite outcome after adjustment for baseline risk. A *p* value less than 0.05 will be considered significant for all tests.

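### One unadjusted 0.05 threshold covers about 29 to 30 co-primary organ metrics and several families of tests, so at least one false-positive finding is likely

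*Protocol article*

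**What the plan says.** The closing sentence of the Statistical plan in the Protocol article sets one threshold: a p "value less than 0.05 will be considered significant for all tests". Study outcomes defines the primary set broadly: "Primary outcomes include patient reported symptom burden and organ injury metrics as assessed by functional performance evaluations, serum biomarkers and MRI tissue characterization". It refers to Table 1 ("Summary of organ injury outcomes"), which lists six organs and names no lead metric and no testing order.

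The Statistical plan puts these metrics through several families of tests:

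- recovered patients v healthy controls ("two sample t-test or Mann–Whitney U test used for continuous variables, as appropriate", with chi-square or Fisher tests for categorical variables);
- one-way ANOVA across four symptom-severity groups, followed by Tukey or Games-Howell pairwise tests;
- Pearson correlations of MRI tissue measures with functional performance;
- a univariable Cox model for each serum and imaging parameter.

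On the lungs, the Magnetic resonance imaging section says that "40 radiomic texture features are computed in three dimensions for each lung". Table 1 carries the radiomics as one lung-lesion entry.

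**The concern.** Tukey and Games-Howell limit error among the pairs of symptom groups for one metric. They do nothing across metrics, organs or families. With all of Table 1 co-primary and each test judged at 0.05, a nominally significant result somewhere is the expected outcome even if infection had no lasting effect on any organ. A reader could not tell such a result from a real one.

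This matters because the Abstract states the overall goal as finding new treatment targets, and the Discussion expects the results to support trials. The severity and correlation tests are the most exposed, since they address the study's own hypothesis. By the account in Sample size calculation, one earlier multi-organ study linked only myocardial T1 to severe symptoms or disability, and another found no link between imaging injury and functional performance. Many of those nulls could be true.

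**Working it through.** The article states no overall error rate, and its target of 200 patients and 100 controls is empirical, so there is no figure of the plan's own to reproduce.

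**Counting the metrics**

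- Functional, 8: the 6 min walk counted once; FEV1 and FVC ("Hand-held spirometry measured forced expiratory volume in 1 s and forced vital capacity during 3 repetitions"); five cognitive tests ("patients completing 5 modules including the Picture Sequence Memory Test").
- Circulating, 9: troponin I, B-type natriuretic peptide, AST, ALT, GGT, LDH, total bilirubin, electrolytes (counted as one) and creatinine.
- MRI, 12 without radiomics: lung water density; LVEF, myocardial T1 and T2; brain volume, lesions and susceptibility/iron; hepatic T1 and T2*; renal T1; muscle T1 and T2*.

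Total 8 + 9 + 12 = 29, or 30 with the lung-lesion entry. Counting table entries without splitting spirometry and cognition gives 25.

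**Counting the correlations**

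- Upper reading, every MRI metric with every functional measure: 12 × 8 = 96.
- Lower reading, pairs matched by organ as in Table 1: lung water × 3 (FEV1, FVC, walk) = 3; cardiac 3 × walk = 3; brain 3 × 5 tests = 15; muscle 2 × walk = 2. Total 23.

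The article does not say which reading applies.

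**Error rates**

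For *m* independent tests with all nulls true, the expected false positives are 0.05*m* and P(at least one) = 1 − 0.95^*m*. P(three or more) is the binomial tail. Sidedness is not stated; the rate is 0.05 per test either way.

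| Tests | *m* | Expected | P(≥1) | P(≥3) |
|---|---|---|---|---|
| One family | 29 | 1.45 | 77% | 18% |
| Patients v controls + severity ANOVA | 29 × 2 = 58 | 2.9 | 95% | 56% |
| As above + 23 correlations | 81 | 4.05 | 98% | 78% |
| As above + 96 correlations | 154 | 7.7 | >99.9% | 98% |

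For one family, 25 or 30 metrics instead of 29 give 72% or 79% for at least one. The Cox models are not counted and would add more tests.

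**Sensitivity to correlation**

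I simulated equally correlated z statistics (40,000 runs). The correlations are assumed, since the article gives none.

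| Assumed correlation | 29 tests: P(≥1) | 58 tests: P(≥1) | 154 tests: P(≥3) |
|---|---|---|---|
| 0.1 | 76% | 93% | 97% |
| 0.3 | 65% | 84% | 82% |
| 0.5 | 50% | 66% | 55% |

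The expected counts do not change.

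**Sensitivity to real differences**

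If only 14 of the 29 nulls in one family were true, the expected count would be 14 × 0.05 = 0.7 and P(≥1) would be 1 − 0.95^14 = 51%.

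**The case against.** **Radiomics.** With 40 features in each of two lungs, a reader might infer 80 more tests, with 80 × 0.05 = 4.0 expected false positives and 1 − 0.95^80 = 98% for at least one. The article does not support that. It says the features are computed, and gives the purpose: "the presence of patchy pathology was identified using an automated quantitative approach employing radiomic analysis of the lung parenchyma". Table 1 has one corresponding entry, so the features may feed a single measure. Texture features of the same lungs are also unlikely to be independent. This objection stands, and radiomics are left out of the counts above. The article does not say, however, how 80 values become one outcome.

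**Near-certainty of several false findings.** A reader might also infer this. It needs all nulls true, independent tests and the larger set of correlations. In one family of 29, three or more has probability 18%. A complete null is doubtful for patients v controls: Table 3 shows hypertension in 24%, diabetes in 13% and COPD in 11% of patients and in none of the controls, and earlier studies reported raised myocardial T1. Real or confounded differences leave fewer true nulls, and multiplicity control does not cure confounding. With two-sided tests, about half of chance patient-control differences would favour patients and would not look like injury. All of this stands and limits the claim.

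**A fuller plan may exist, and the study is observational.** A condensed article may leave detail to an unseen analysis plan, and how strictly to adjust such work is partly judgement. The 0.05 sentence can also accommodate adjusted p-values, as it must for Tukey and Games-Howell. But the article does not leave the threshold open: it fixes one for all tests and names adjustment only within a metric. As written, the rule inflates false positives when followed.

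**Conclusion.** The concern holds in limited form. About 29 to 30 metrics are co-primary without a hierarchy, every test is judged at 0.05, and no control across metrics or families is stated. Assuming all nulls true and independence, expected false positives run from 1.45 (one family) through 2.9 (both group comparisons) to between 4.05 and 7.7 (with correlations). The matching chances of at least one are 77%, 95%, and 98% to over 99%. Correlation lowers those chances but not the counts; true or confounded differences lower both. At least one false-positive finding is likely and several are plausible across families. The article does not support the statement that several are near certain, or that the lung radiomics will by themselves produce positive findings.

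**What to change.** Replace the blanket 0.05 sentence in the Statistical plan with Benjamini-Hochberg false discovery rate control at 5% within each stated family of Table 1 metrics:

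1. patients v controls;
2. the omnibus ANOVA across symptom severity, keeping Tukey or Games-Howell within each metric;
3. MRI-function correlations, with the pairs to be tested listed.

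Report unadjusted p-values alongside as descriptive. Enter the radiomics as the single lung-lesion outcome of Table 1 or, if features are tested individually, as a separate false-discovery family labelled exploratory.

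Naming a lead MRI metric per organ with Holm control is optional and a larger change. It would have to be fixed before analysis, and it would demote other outcomes now listed as primary. The comparison of moderate-to-severe patients with controls, which is in the objective at the end of the Introduction but not among the planned tests, would also have to be added to the Statistical plan.

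The main change works on p-values already planned and needs no new data. Its cost is a stricter threshold for individual metrics and so some loss of power. No stated power figure is affected, because the sample size is empirical.

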### Sample size calculation

There is little data informing on associations between symptom burden, functional performance and MRI derived tissue composition in patients with recovered COVID-19. At the time of our study conception, only one MRI study reported on 100 patients at a median of 71 days from COVID-19 illness and found increased native myocardial T1 compared to 50 healthy controls, median 1,125 ms vs. 1,082 ms, respectively. They also reported increase myocardial T1 in those with prior hospitalization (*N* = 33) compared to patients who had recovered at home (*N* = 67), median 1,141 ms vs. 1,119 ms, *p* = 0.008 (16). A subsequent multicenter study of 148 patients with prior hospitalization for severe COVID-19 also found increased myocardial T1 compared to 40 healthy volunteers, mean 1,033 ms vs. 1,008 ms, *p* < 0.001 (17). However, data linking imaging to symptoms and functional performance is inconclusive. In a multi-organ, MRI based study of 201 patients with long COVID, only abnormalities in myocardial T1 were associated with severe symptom burden and/or disability (14). A multisystem, MRI-based study of 54 patients with prior hospitalization for severe COVID-19 found that imaging derived organ injury (cardiac, renal and hepatic T1 and brain T2*) was associated with circulating biomarkers of inflammation but not with functional performance (spirometry, 6MWT and cognitive testing) (13). Given the lack of data on potential associations of MRI tissue characterization with symptom burden and/or functional performance at the time, we empirically established a target of 200 patients with recovered COVID-19 and 100 age- and sex-matched healthy controls without prior infection. Clinical characteristics of the study population are presented in Table 3.

**Table 3 tab3:** Clinical characteristics.

	Recovered COVID-19	Healthy controls
Number of patients	215	133
Female, (%)	139 (65%)	68 (51%)
Age	51 (14)	47 (15)
Caucasian race, (%)	170 (79%)	113 (85%)
Height, cm	168 (10)	170 (9)
Weight, kg	83 (20)	72 (13)
Systolic blood pressure, mmHg	134 (18)	122 (13)
Diastolic blood pressure, mmHg	84 (11)	80 (9)
Heart rate, bpm	71 (12)	73 (13)
Oxygen saturation (%)	98 (2)	98 (2)
**MEDICAL HISTORY**		
Current smoker, (%)	9 (4%)	1 (1%)
Past smoker, (%)	50 (23%)	8 (6%)
Alcoholic beverages/week	1.8 (2.6)	3 (4)
Hypertension, (%)	51 (24%)	0
Diabetes mellitus, (%)	28 (13%)	0
Dyslipidemia, (%)	38 (18%)	0
Alcohol overuse, (%)	2 (1%)	0
Coronary artery disease, (%)	4 (2%)	0
Heart failure, (%)	1 (0.5%)	0
Atrial fibrillation (%)	4 (2%)	0
COPD, (%)	23 (11%)	0
Sleep apnea, (%)	14 (7%)	0
Stroke, (%)	5 (2%)	0
Cognitive impairment, (%)	3 (1%)	0
Neuropathy, (%)	7 (3%)	0
Renal insufficiency, (%)	7 (3%)	0
Liver disease, (%)	0	0
Prior cancer, (%)	17 (8%)	0
Pneumonia in last year, (%)	2 (1%)	0
**COVID-19 Illness**		
Duration of Illness		
1–7 days, (%)	80 (37%)	Not applicable
8–14 days, (%)	68 (32%)	
>14 days, (%)	67 (31%)	
Hospitalized, (%)	59 (27%)	
Intensive care unit, (%)	17 (8%)	
Ventilation, (%)	11 (5%)	

Values are represented as total number (%) or mean (standard deviation).

### Supplementary studies

Between May and October 2021, patients from the recovered COVID-19 group were contacted via phone and email and invited to participate in supplementary studies of energy metabolism and patient perspectives. Based on emerging data and observations, these sub-studies were opportunistically conceptualized after the primary study had been initiated. In the supplementary study on energy metabolism, a subset of patients were examined to investigate the role of the most metabolically active organs affecting resting energy expenditure (REE). Notably, organs significantly influence REE, accounting for approximately 75% of this energy metabolism component. Given the systemic effects of COVID-19, understanding potential changes in energy metabolism post-recovery is imperative due to its impact on body composition and nutritional status in general (34–36). By examining the impact of individual organs on REE in those recovered from COVID-19, we aim to gain insights into the lasting metabolic effects of infection, distinct from its acute complications. Knowledge gained could optimize health in the post-recovery phase by guiding targeted interventions. Exclusion criteria for this supplementary study included pregnancy or lactation, having any electronic implant and those who are claustrophobic. Specific protocols were followed for REE assessment as described previously (37). Participant’s REE were assessed using a metabolic cart with ventilated hood system (Vmax^®^ Series, CareFusion, Yorba Linda, CA, United States) at the Human Nutrition Research Unit (University of Alberta, Edmonton, AB, Canada).

Abnormalities in energy metabolism will be explored compared to commonly used equations. A new approach will be tested to evaluate the resting metabolic rate *K*(*i*) values of major organs (liver, heart, lungs, kidneys and brain) and tissues on the basis of a mechanistic model: REE = Σ(*K*(*i*) × *T*(*i*)), where REE is whole-body REE measured by indirect calorimetry, and *T*(*i*) is the mass of individual organs and tissues measured by MRI. With measured REE and *T*(*i*), marginal 95% confidence interval for *K*(*i*) values will be calculated by stepwise univariate regression analysis (38).

For the supplementary study on patient experiences, we sought to learn about the individual experience of acute and recovered COVID-19 and to determine if patient reported symptoms and experiences correlated to physiologic testing. An audio-taped 45-to-60-min interview was conducted, using an open-ended style. The researcher recorded field notes after each interview, including general observations, any important nonverbal communication, and thoughts or feelings regarding the interview *(“memoing”).* The data collected was transcribed verbatim and stripped of potential identifiable material by a professional transcription company.

For the analysis, a broad-based data coding system will be created and considered in contrast to other groupings with different properties. These initial codes will then be developed into concepts, themes, and potential sub-themes, into what is termed “pattern recognition.” The final synthesis of the data will be achieved when the researcher has reached a level of interpretation that develops a conceptual definition that will be meaningful and relevant to applied practice.

## Discussion

The primary goal of this study is to improve knowledge of the mechanisms governing disability and poor health in patients with persistent COVID-19 symptoms. We have therefore undertaken a comprehensive multiparametric assessment of post-COVID-19 sequelae in a large cohort of survivors and healthy controls. Novel aspects include a comprehensive MRI-based characterization of body composition and detailed measures of functional impairment. The results from this study could inform on potential therapeutic targets for long COVID syndrome including post-COVID related cardiovascular risk. Long COVID continues to affect approximately 10% of patients infected with the Omicron variant (5, 39). Therefore, these results could inform on current practice and provide justification for clinical trials of long COVID.

### Ethics and dissemination

Given the observational nature of this study, ethical and safety concerns are minimal. Serum samples and imaging data are stored at secure repositories at the University of Alberta. Requests for access to data will be provided upon reasonable request where permissible by institutional governance. Results from this trial will be disseminated through presentation at scientific meetings, manuscript publications, knowledge translation activities with national and international societies and incorporation into clinical guidelines. We will actively engage patient groups through public speaking engagements facilitated by long COVID networks. Long COVID groups are also active on social media and we will disseminate results through these platforms.

## Ethics statement

The studies involving humans were approved by the University of Alberta and the University of Calgary Health Research Ethics Boards. The studies were conducted in accordance with the local legislation and institutional requirements. The participants provided their written informed consent to participate in this study.
